**Figure 1 pul212337-fig-0001:**
[figure not shown]
Dose escalation and de‐escalation protocol. Bd, twice daily; CMR, cardiac magnetic resonance imaging; ERA, endothelin receptor antagonist; OPA, oral IP‐receptor agonist; PAH, pulmonary arterial hypertension; PDE5i, phosphodiesterase type‐5 inhibitor; sGCS, soluble guanylate‐cyclase stimulator; tds, three times daily; WHO FC, World Health Organization Functional Class.

As per standard practice, the treatment schedules will include a minimum PDE5i washout period of 24–48 h (depending on PDE5i) before initiation of riociguat^12^; in addition, riociguat and selexipag will be titrated according to established dose‐adjustment schemes to maximum doses of 2.5 mg three times per day, and 1600 μg twice daily, respectively as tolerated (Figure 1).

In brief, patients in Arm A will initiate treatment with selexipag for uptitration to maximal therapy. Before crossover, patients will undergo selexipag dose de‐escalation and washout, followed by PDE5i washout. Patients will then initiate treatment with riociguat for uptitration to maximal therapy. Patients in Arm B will have an initial PDE5i washout period before commencing treatment with riociguat. This will be followed by de‐escalation and washout, and initiation of treatment with PDE5i before crossover to selexipag treatment. In both arms, the primary endpoint evaluation will be undertaken following a minimum intended duration of 5 weeks on the maximal tolerated dose of each therapy. The dose escalation and de‐escalation protocol are shown in Supporting Information: Table S2.

### Clinical assessments

Patients will undergo clinical assessments at baseline before receiving study drug treatment, and at Weeks 12 and 27 of the treatment schedule (Figure 1); these will include hemodynamics, 6MWT, MRI, and NT‐proBNP assessments.

MRI analysis will be provided by a study‐appointed core lab using certified clinicians; scans will be deidentified and analyzed in random order independent of patient and time point. Analysis of primary and secondary endpoints will be undertaken in a blinded manner by an independent statistical team in accordance with a pre‐specified statistical analysis plan.

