CardioMEMS™ HF System (Abbott) is a wireless, PAP monitor implanted at the time of right heart catheterization to provide remote measurement of cardiopulmonary hemodynamics. CardioMEMS is approved for routine clinical practice in the USA and Europe, and to date over 30,000 of these monitors have been implanted. The Confirm Rx™ ICM (Abbott) is a minimally invasive regulatory‐approved cardiac monitor, implanted in a clinical setting for patients who experience unexplained symptoms, such as dizziness; palpitations, chest pain, syncope, shortness of breath, as well as for patients who are at risk for cardiac arrhythmias. Over 40,000 Confirm RX™ have been implanted and the device is in routine clinical use in the United Kingdom.

Here, we detail the protocol for a study in which patients with PAH, established on guideline‐recommended dual oral therapy and evaluated as intermediate‐low risk,^29^ will be implanted with CardioMEMS and ICM devices. Following implantation, patients will enter a 2 × 2 crossover study in which PDEi will be replaced with sGCS (ERA + sGCS), or an IP receptor agonist will be added to PDEi and ERA (PDEi + ERA + IP receptor agonist). Data obtained from remote monitoring will be compared with that from established clinical investigations undertaken at baseline and maximal therapy on each drug. The crossover design of this study, which will incorporate structured up‐titration of these drugs, is aimed at evaluating the capacity of implantable technology for early evaluation of the clinical efficacy of these drugs. A crossover study is a logical study designed to investigate the intra‐patient efficacy of these treatment options and increase the power to detect clinical efficacy. Additionally, the study will provide insight into the capacity of remote monitoring technology to facilitate trials that are not currently possible due to the requirement for repeated, hospital‐based invasive/imaging procedures.

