### Objectives and endpoints

The main aims of this study will be to assess the individual difference in effect between treatment escalation with selexipag (PDEi + ERA + IP receptor agonist) or riociguat (riociguat; ERA + sGCS) on RV stroke volume (flow) as measured by cardiac MRI in patients with intermediate‐low risk PAH, and to determine whether remote monitoring devices can be used to provide an early assessment of clinical efficacy of drug therapies for PAH.

The primary endpoint will be change in RVSV (flow) measured by MRI from baseline to 12 weeks for each therapeutic strategy. Change in RVSV provides a robust, objective assessment of clinical efficacy and will represent a clinically meaningful change in physiology.^31^ ESC guidelines recommend follow‐up at 3–6 months after a change in therapy. Titration protocols mimic standard clinical care and expected time‐to‐improvement.^2^

Secondary endpoints for each therapeutic strategy include change from baseline to 12 weeks in hemodynamics (total peripheral resistance [TPR], mean pulmonary artery pressure [mPAP], cardiac output [CO], cardiac index, stroke volume [SV], heart rate [HR]), 6MWT, NTpro‐BNP, MRI parameters (RVEF, right ventricular end‐systolic volume [RVESV], right ventricular end‐diastolic volume [RVEDV], RVSV (volume), left ventricular ejection fraction [LVEF], left ventricular end‐systolic volume [LVESV], left ventricular end‐diastolic volume [LVEDV], and LVSV flow), quality of life (EmPHasis‐10), medication compliance (PHoenix PRO) and side effects, depression and anxiety symptoms (Generalized Anxiety Disorder‐[GAD]‐2/7 and Patient Health Questionnaire [PHQ]‐2/9), WHO functional class, and activity levels as measured with a Garmin Venu2 smartwatch. A full list of outcome measures is provided in Table 1.

**Table 1 pul212337-tbl-0001:** Outcome measures.

	Hospital‐based measures	Remotely monitored measures
Primary outcomes	Change in RVSV (flow) measured by MRI	

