#### Statistical analysis plan

All statistical analysis plans (SAPs) will be drafted early in the study and finalized before the analysis of unblinded data.

The primary clinical efficacy analysis will use a linear mixed effects model with the dependent variable being the change in RVSV (flow) from baseline to 12 weeks. “Baseline” and “12 weeks” refer to the time points within each treatment period. Each participant will contribute up to two observations if they complete both treatment periods. A random effect for each participant will be included together with the within‐treatment period baseline RVSV (flow) measurement, a fixed period effect, and treatment (selexipag or riociguat) allocated during the treatment period. This model will be used to estimate the mean difference between the two treatment approaches (ERA + sGCS and PDEi + ERA + IP receptor agonist), together with a 95% confidence interval and a *p* value using a Wald test.

Similar methods will be applied to the analysis of secondary efficacy outcomes. Treatment effect heterogeneity between subgroups will be assessed by including treatment‐by‐subgroup interaction terms in regression models. Main analyses will use complete data only, but multiple imputation will be used for missing data in sensitivity analyses. No adjustments will be made for multiple statistical tests. All efficacy analyses will follow the intention to treat principle (i.e., analysis according to randomized treatment, regardless of treatment compliance). Safety data (adverse events and side effects) will be summarized in relation to treatment being received at the onset of the event, and the study period (pretreatment period 1, treatment period 1, washout period, treatment period 2, posttreatment period 2); no formal statistical comparisons will be applied.

To analyze whether changes in RVSV (flow) may be explained by remotely monitored physiological parameters, we will test whether there is a significant correlation between the change between baseline and Week 4/Week 8 physiological parameters and the change between baseline and Week 12 RVSV (flow) outcome. We will also adopt a mediation analysis approach to investigate what proportion of the change between baseline and Week 12 RVSV (flow) is explained by the change between baseline and Week 4/Week 8 physiological parameters using the mediation package in R. Secondary endpoints will be analyzed using appropriate regression models.

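### The primary model needs an MRI baseline in each treatment period, but the stated assessment schedule gives only one, so the two sections must be reconciled

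*Protocol article*

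**What the plan says.** The primary endpoint (Objectives and endpoints) is the "change in RVSV (flow) measured by MRI from baseline to 12 weeks for each therapeutic strategy". The Statistical analysis plan section says that the terms for baseline and 12 weeks "refer to the time points within each treatment period", and that each participant supplies up to two change scores. The linear mixed model has a random participant effect and, as fixed terms, the within-treatment "period baseline RVSV (flow) measurement, a fixed period effect, and treatment (selexipag or riociguat) allocated during the treatment period". It adds: "Main analyses will use complete data only", with multiple imputation kept for sensitivity analyses.

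The Clinical assessments section gives the schedule: "Patients will undergo clinical assessments at baseline before receiving study drug treatment, and at Weeks 12 and 27 of the treatment schedule". It goes on: "these will include hemodynamics, 6MWT, MRI, and NT‐proBNP assessments". The Treatment section describes de-escalation and washout before crossover and mentions no scan there. The Introduction speaks of "established clinical investigations undertaken at baseline and maximal therapy on each drug".

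**The concern.** A change from the start of period 2 needs a scan taken after washout and before the second drug. The stated schedule has none: one scan precedes all study drug, and the other two fall at Weeks 12 and 27. Taken at its word, that schedule leaves every participant without the period-2 outcome and without the period-2 covariate. The clinic-based secondary endpoints (hemodynamics, 6MWT, NT-proBNP) have the same problem, because similar methods are planned for them.

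The analyst would then have to choose a remedy that the document does not specify, in an open-label trial. Two obvious choices do harm. Dropping the incomplete rows discards the crossover. Using Week 12 as the period-2 baseline sets the second drug against the on-drug result of the first.

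**Working it through.** **1. Count of scans.**

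| Source in the protocol article | MRI occasions | Count |
|---|---|---|
| Statistical analysis plan: baseline and 12 weeks in each of two periods | 2 × 2 | 4 |
| Clinical assessments: pre-drug baseline, Week 12, Week 27 | 1 + 2 | 3 |

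If Week 27 is the 12-week point of period 2, that period starts at 27 − 12 = Week 15, three weeks after the Week 12 visit. Week 15 is an inference; the document does not state it. No MRI is listed there. If Week 27 were instead the period-2 baseline, the period-2 endpoint would be missing.

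**2. The plan's own power figure.** Inputs from Sample size calculation: difference 12 mL, within-patient SD 16.5 mL, 40 participants, two-sided 5%.

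- SE = 16.5 × √(2/40) = 3.69 mL
- 12 / 3.69 = 3.25
- Power = Φ(3.25 − 1.96) = 90.2% (88.7% with a t distribution on 38 df)

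The stated 90% reproduces. It assumes one usable outcome per treatment from each of the 40 participants and does not reveal which baseline was intended.

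**3. One common baseline.** If both changes are taken from the same pre-randomisation scan b, the within-patient contrast is (y₁ − b) − (y₂ − b) = y₁ − y₂. The baseline cancels. In a simulated data set the estimate was 11.55 mL both from change scores and from post-treatment values alone. The SE therefore stays at 3.69 mL.

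**4. Period-2 rows dropped.** This leaves 20 v 20, adjusted for the pre-drug scan. With intraclass correlation ρ (an assumption; the document gives none), the residual SD is 16.5 × √(1 + ρ) and SE = residual SD × √(2/20). Power is for a two-sided t test.

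| ρ (assumed) | Residual SD (mL) | SE (mL) | Power for 12 mL |
|---|---|---|---|
| 0.3 | 18.8 | 5.95 | 50% |
| 0.5 | 20.2 | 6.39 | 45% |
| 0.8 | 22.1 | 7.00 | 39% |

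Even with the residual SD held at 16.5 mL, power would be 63% (normal approximation).

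**5. Week 12 used as the period-2 baseline.** Let A and B be the true effects of the two drugs.

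- Sequence A then B: the changes are A and B − A, so period 1 minus period 2 is 2A − B.
- Sequence B then A: the changes are B and A − B, so period 1 minus period 2 is 2B − A.
- Estimate = 0.5 × [(2A − B) − (2B − A)] = 1.5 (A − B).

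A true 12 mL would appear as 18 mL. That is the unadjusted result. The planned model adjusts for baseline, which reduces the bias. Simulating it (random intercept, period, treatment, baseline; 40 participants; 12 mL; within-patient SD 16.5 mL) gives a multiplier of about 1.15 at ρ = 0.3 and about 1.4 at ρ = 0.8, so 12 mL would appear as about 14 to 17 mL. Separate runs differ by a few hundredths.

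**The case against.** The strongest objection is that the governing schedule is not in view. The Clinical assessments section points to Figure 1, whose legend defines an abbreviation for cardiac MRI, and Study design places the summary of all visits in Table S1. Either could list a scan before period 2. A condensed article may leave such detail to them. The baseline in Clinical assessments, and the Introduction's wording, could also be read as one baseline per drug, though that is not the natural reading of a list that ends with Weeks 12 and 27.

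Much of this stands. A reader might infer that the period-2 change cannot be computed in this trial; the documents do not support that. They show only that it cannot be computed on the schedule as stated. The drug contrast itself remains estimable from Weeks 12 and 27. The objection does not remove the conflict: both statements are explicit, and one needs correcting whatever the figure and table show.

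A reader might also infer that a period-2 baseline would be on different background therapy in the two arms. The Treatment section does not fix when such a scan would be taken. A scan between Arm A's two washouts, and one after Arm B restarts PDE5i, would both be on PDE5i plus ERA. That inference is not supported.

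Finally, nothing in the document proposes Week 12 as a baseline or intends to discard period 2; it expects up to two observations per participant. The power loss and the inflation are consequences of possible repairs, not of the plan as intended.

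**Conclusion.** The point holds as an internal conflict about the primary analysis: four MRIs are needed by the model and three are listed. On the listed schedule, the period-2 outcome and covariate are undefined. Whether the fourth scan exists depends on Figure 1 and Table S1, which must be reconciled with both sections.

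The stated 90% power is not in error. It survives if Weeks 12 and 27 are compared directly or against one common baseline. It falls to about 39–50% only if period-2 rows are dropped, at an assumed intraclass correlation of 0.8 to 0.3. The 1.5-fold inflation applies only to an unadjusted change analysis with Week 12 as baseline; for the planned baseline-adjusted model the range is about 1.15 to 1.4 under the same assumed correlations. The analysis plan can settle the definition, but it cannot supply a scan that was not taken.

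**What to change.** Check Figure 1 and Table S1, then take one of two branches.

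(a) If an MRI before period 2 is scheduled, add it to the Clinical assessments section. The endpoint and model can stay. The cost is a correction of wording.

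(b) If it is not, redefine the primary analysis as end-of-period RVSV (flow) at Weeks 12 and 27, with a participant random effect, period and treatment, and the single pre-randomisation MRI as the baseline covariate. Change from that common baseline in both periods is equivalent. Remove the within-period definition of baseline, and apply the same rule to the clinic-based secondary endpoints. This changes the primary analysis, so it needs a documented amendment before unblinded data are analysed, but no extra scan, visit or participant. It keeps the 3.69 mL standard error.

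In either branch, state that the Week 12 scan must not serve as the period-2 baseline, because it is an on-drug value of the other treatment.

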### Remote monitoring

Physiological parameters to be monitored will include TPR, mPAP, CO, SV, and HR (Table 1). Patients will be given instructions on how to take readings at the time of implantation. In addition, remote detection of changes in physical activity levels will be measured by Garmin Venu2 smartwatch, and the 6‐min walk test (6MWT) performed at home.

### Patient‐reported outcomes

To date, no published randomized controlled trials in PAH have undertaken PAH‐specific PRO instruments as secondary endpoints (Figure 2). The current study aims to understand patients' attitudes about PAH medications and the impact of the study medication on quality of life, as well as explore attitudes about the use of remote technologies.

**Figure 2 pul212337-fig-0002:**
[figure not shown]
Primary outcomes in landmark PAH randomized controlled trials with patient‐reported outcomes included as secondary endpoints. DFI, dyspnea fatigue index; EQ‐5D, EuroQoL five‐dimension; MLWH, Minnesota Living with Heart Failure questionnaire; M&M, morbidity and mortality; PAH, pulmonary arterial hypertension; PRO, patient‐reported outcome; PVR, pulmonary vascular resistance; SF‐36, Short‐Form 36; Exercise endpoint inclusive of 6‐min walk distance and actigraphy; ^a^Living with Pulmonary Hypertension (LPH) questionnaire was undertaken in PATENT‐1; however, this was considered exploratory.

Quality of life outcomes will be assessed weekly using the validated EmPHasis‐10 questionnaire.^34^ Validated questionnaires will be used twice monthly to screen for anxiety (GAD‐2)^35^ and depression (PHQ‐2) symptoms.^36^

Patients will also be asked to record, on a weekly basis, any side effects of the study medications and to track dose–response changes that are observed. Data will be collected on patients' attitudes toward their PAH medications and patient‐reported medication compliance (PHoenix PRO questionnaire; Supporting Information: Figure S1). All participants will be invited to co‐enroll in the COHORT‐digital study,^37^ which enables PRO reporting through a mobile application called Atom5™ (Figure 3). If participants decline to co‐enroll for digital PRO reporting, data for these outcomes will be collected using a 10‐item questionnaire via telephone communication into the eCRF.

**Figure 3 pul212337-fig-0003:**
[figure not shown]
Patient‐reported outcomes in the PHoenix study. A, Arm A = riociguat/selexipag and B, Arm B = selexipag/riociguat GAD, Generalized Anxiety Disorder questionnaire; PHQ, Patient Health Questionnaire.

Additionally, patients will also be asked to provide their insight to help understand attitudes regarding remote monitoring, clinical care, and health outcomes at enrollment and study completion.

### Safety

Adverse events (AEs) will be monitored over the duration of the study period; AEs that are definitely or possibly related to the device or the insertion procedure should be considered device‐related (adverse device effect [ADE]).

### Statistical analyses

#### Sample size calculation

The sample size was chosen to ensure adequate power to detect differences in the clinical efficacy of the two treatment approaches in population‐level analyses and to have adequate power to evaluate the ability of implantable/remote technology to provide early evaluation of such clinical efficacy. For comparing the clinical efficacy of the two treatment approaches, we have used published RVSV data reporting a minimal clinically important difference of 12 mL and within‐patient standard deviation (SD) of 16.5 mL.^38^ The current study will be powered using a standardized effect (SE) of 12/16.5 = 0.73. Assuming 1:1 randomization of the participants to the two treatment sequences, 40 participants will provide 90% power in the population‐level clinical efficacy analysis for a 5% two‐sided type‐I error rate, with SE of 0.73. This is below the SE previously reported for the pulmonary vascular resistance (PVR; SE = 353.4/219.0 = 1.61),^3^ and the RVEF (SE = 9.12/7.39 = 1.23)^20^ and comparable to that observed for the 6MWT (SE = 36.0/46.7 = 0.77).^6^ Therefore, the study will be well‐powered for population‐level analyses of these additional important outcomes.

The sample size of 40 also provides good power for assessing whether changes in remote physiological measures from baseline to 4 and 8 weeks (mPAP, CO, HR, and heart rhythm) are correlated with changes in clinical measures from baseline to 12 weeks. The sample size of 40 patients provides 90% power, at a two‐sided 5% type‐I error rate, for correlations greater than 0.5, which would represent those of clinical interest.

The study is not powered for formal mediation analysis, so this will be considered exploratory. No formal multiple‐testing correction will be applied.

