Selexipag, an IP receptor agonist, improves the time‐to‐clinical‐worsening in patients on a range of background therapy regimens (including patients on no therapy [20.4%]; ERA or PDE5i monotherapy [47.1%]; and ERA/PDE5i dual therapy [32.5%]).^4^ However, data suggest that initiating triple therapy (PDE5i/ERA/IP receptor agonist) compared with dual therapy (PDE5i/ERA) in newly diagnosed treatment naïve patients offers no significant improvement in snapshot hemodynamic measurements or exercise capacity.^11^ Additionally, switching PDE5i for another drug targeting the NO pathway (riociguat, an sGCS) improves disease severity as assessed by World Health Organization (WHO) functional class and 6MWT distance, and reduces clinical worsening events compared with continuing PDE5i therapy.^12^ In all regulatory approval studies, significant side effects and therapeutic non‐adherence were observed.^4^, ^6^, ^12^, ^13^, ^14^, ^15^, ^16^, ^17^, ^18^

In clinical practice, response to therapy and/or assessment of disease progression is made by assessing pressure and flow during invasive right heart catheterization, by monitoring the downstream effect on right heart structure and function, and by evaluating exercise capacity. European Society of Cardiology (ESC) guidelines recommend invasive assessment of cardiopulmonary hemodynamics for disease diagnosis, assessment of severity, and to inform treatment decisions (therapeutic change and transplant).^2^ Other recommended means of guiding treatment decisions include regular measurement of exercise capacity by 6MWT, disease‐specific risk scoring, assessment of right heart strain by N‐terminal pro‐brain natriuretic peptide (NT‐proBNP), and/or noninvasive imaging, with magnetic resonance imaging (MRI) acknowledged to be more accurate than echocardiography.^2^

The currently established standard for phase 2 studies of PAH therapies includes the assessment of invasive hemodynamics and the 6MWT.^1^ However, recent studies have demonstrated that noninvasive endpoints, such as right ventricular ejection fraction (RVEF) and right ventricular stroke volume (RVSV) measured by MRI, are repeatable, and detect treatment change in a manner similar to invasive catheterization and NTpro‐BNP, thereby establishing MRI as a robust, objective, noninvasive assessment of treatment response in patients with PAH.^19^, ^20^

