### Study population

The study aims to recruit 40 patients with PAH, established on PDE5i and ERA, through the UK National Pulmonary Hypertension Clinical Studies Network (UNIPHY)—a collaboration of UK centers commissioned for the treatment of PAH, providing access to all patients within the UK currently receiving targeted therapy for PAH (>5000).^32^, ^33^ Suitable patients will be identified from existing patient lists by local teams and invited to screening via clinical and research teams.

Eligible patients meeting the inclusion and exclusion criteria (Table 2) will be established on PDE5i/ERA dual therapy and will meet NHS England's National Commissioning and ESC guideline criteria for initiation of IP receptor agonist or sGCS.^2^, ^9^, ^10^ While it is expected the majority of patients recruited will have intermediate‐low risk PAH, patients with intermediate‐high risk PAH who decline intravenous therapy will also be considered.

**Table 2 pul212337-tbl-0002:** Summary of eligibility criteria.

**Inclusion criteria:** 1. Able to provide informed consent 2. Age 18–80 years 3. PAH which is idiopathic, heritable, or associated with drugs, toxins, or connective tissue disease 4. Stable PAH therapeutic regime comprising any combination of ERA and PDE5i for at least 1 month before screening (unless unable to tolerate therapy) 5. WHO functional class III 6. Resting mPAP ≥20 mmHg, pulmonary capillary wedge pressure ≤15 mmHg, pulmonary vascular resistance ≥2 Wood Units measured by right heart catheterization at time of diagnosis 7. 6MWT > 50 min at entry 8. eGFR > 30 mL/min/1.73 m² at entry 9. Inadequate treatment response (clinically determined)

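### The 90% power is a no-loss figure for 40 patients completing both periods, and the claim of good power for PVR, RVEF and 6MWT does not follow from the effects cited

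*Protocol article*

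**What the plan says.** The Sample size calculation section starts from a "minimal clinically important difference of 12 mL" and a within-"patient standard deviation (SD) of 16.5 mL". It concludes that "40 participants will provide 90% power" at a "5% two‐sided type‐I error rate, with SE of 0.73", where SE is the article's abbreviation for standardized effect. The Study population section gives the same number as the recruitment target: "The study aims to recruit 40 patients with PAH".

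Under Statistical analysis plan, each participant gives at most two observations, and two only if both periods are completed. A random participant effect is fitted, and the treatment difference is tested with a Wald test. On missing data: "Main analyses will use complete data only", with multiple imputation as a sensitivity analysis.

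The sample size section then sets the primary standardized effect beside published values for PVR (353.4/219.0 = 1.61), RVEF (9.12/7.39 = 1.23) and 6MWT (36.0/46.7 = 0.77). From these it infers that the trial is well powered for population-level "analyses of these additional important outcomes". It also states 90% power with 40 patients for correlations above 0.5.

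**The concern.** Two statements describe properties that the design does not have as written.

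First, the number recruited and the number powered are both 40, so nothing is set aside for patients who do not complete. Each patient has to get through two titrations, the washouts between them, and MRI at Weeks 12 and 27. The Introduction notes tolerability problems with these drug classes: "In all regulatory approval studies, significant side effects" and non-adherence were seen.

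Second, power for a secondary outcome here means power to detect a difference between two active strategies. A published effect of a therapy says little about how far two therapies differ, least of all when the Introduction states equipoise between them.

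If both statements stand, a null result, above all on 6MWT, could be read as better evidence of no difference than it is.

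**Working it through.** **Inputs** (Sample size calculation): difference 12 mL, within-patient SD 16.5 mL, two-sided 5%, N = 40, 1:1 to two sequences. Normal quantiles: 1.960 for alpha and 1.282 for 90% power, sum 3.2415.

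**Reproducing the 90%.** In a 2 × 2 crossover with N completers, the standard error of the treatment difference is 16.5 × √(2/N).
- N = 40: 16.5 × √(2/40) = 3.690; 12/3.690 = 3.252; Φ(3.252 − 1.960) = 0.902. The stated figure is right.
- N needed for 90%: 2 × (16.5 × 3.2415/12)² = 39.73, rounded up to 40.
- With 39 completers power is 0.895, so there is no slack.

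Two other readings do not give 90%: 16.5 as the SD of paired differences gives 0.996, and parallel groups of 20 give 0.633.

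**Effect of loss.** The article gives no rate; 10% and 20% are assumptions. For non-completers who keep period 1, I used generalized least squares with a random participant effect, known variances, loss balanced between sequences, and intra-patient correlation from 0.9 down to about 0.

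| Completers | Others contribute nothing | Others contribute period 1 |
|---|---|---|
| 40 | 0.902 | – |
| 36 (10% loss) | 0.870 | 0.872 to 0.887 |
| 32 (20% loss) | 0.829 | 0.833 to 0.870 |

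**Correlation statement.** By Fisher z, power is Φ(atanh(0.5) × √(n − 3) − 1.960).
- n = 40: 0.916.
- n = 38: 0.5493 × √35 = 3.250, giving Φ(1.290) = 0.901.
- n = 36: 0.884.
- n = 32: 0.841.

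So 90% needs about 38 patients with a usable pair of changes.

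**What the cited effects measure.** The Introduction cites the references behind the PVR and 6MWT figures among those for improvements with approved therapies in phase 2/3 studies. It cites the RVEF reference for the ability of MRI to detect treatment change. The Discussion describes this trial as the first evaluation of an sGCS and an IP agonist. On the article's own account, then, these are not selexipag-versus-riociguat differences.

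**Detectable between-strategy difference at N = 40, 90% power.** In SD units it is 3.2415 × √(2/40) = 0.725. If the cited SDs are within-patient SDs like the 16.5 mL (an assumption):
- 6MWT: 0.725 × 46.7 = 33.8, or 94% of the cited 36.0.
- RVEF: 0.725 × 7.39 = 5.4, or 59% of 9.12.
- PVR: 0.725 × 219.0 = 159, or 45% of 353.4.

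If the strategies differed by half the cited effects (illustrative only), power would be 0.41 for 6MWT, 0.79 for RVEF and 0.95 for PVR.

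**Endpoint check.** PVR appears in neither the secondary endpoint list nor Table 1; both list TPR.

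**The case against.** The best defence is that nothing is miscalculated. The 90%, the four ratios and the correlation power all reproduce, and the article never claims 90% after attrition. All of that stands.

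Several stronger readings are tempting, and the document does not support them.
- A reader might put power at 88.7% before any loss, using a t distribution with 38 df, and at 80–85% with 10–20% loss. The plan names a Wald test, which the normal calculation matches. The mixed model also keeps patients who have only period 1.
- A reader might treat the reported side effects and non-adherence as forecasts of missing MRIs. Doses are titrated as tolerated, the endpoint is taken at the maximal tolerated dose, and analysis follows intention to treat. A patient with side effects can therefore still supply data.
- A reader might say that the same loss takes the correlation analysis below 90%. A patient lost after period 1 still gives a pair of changes, so this happens only if more than two patients give no usable pair.

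On the secondary outcomes, the article does not say what kind of SD 219.0, 7.39 and 46.7 are. If they were SDs of paired differences, the detectable 6MWT difference would be 3.2415/√40 × 46.7 = 23.9 (66% of 36.0), and half-effect power would be about 68% for 6MWT and 97% for RVEF. It is also fair that secondary endpoints are defined as change within each strategy, for which therapy effects are relevant. But the analysis section applies methods similar to the primary between-strategy model to them.

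The planned confidence interval gives some protection against misreading a null result. The full protocol may discuss attrition, but this article fixes both the recruited and the powered number at 40.

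**Conclusion.** The point holds as a matter of wording, with moderate consequences. The 90% is correct for 40 completers and is presented as the power of a trial recruiting 40. With 10–20% non-completion (assumed), power falls to about 83–89%, depending on whether non-completers supply period 1 and on the intra-patient correlation. That is a modest loss and does not make the primary comparison underpowered.

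The inference about other outcomes does not follow, because it carries effects of therapy over to a comparison of two therapies. That these are therapy effects is inferred from how the article cites its sources. Subject to the SD assumption, the overstatement is clear for 6MWT, moderate for RVEF and slight for PVR. Naming PVR is a separate slip, since it is not a listed outcome.

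**What to change.** Keep N = 40 and change the sample size text.
1. State that the 90% assumes 40 patients completing both periods, and give the power at the expected number of completers under the planned mixed model and Wald test, with the loss rate named as an assumption.
2. Note that the 90% for a correlation of 0.5 needs about 38 patients with a usable pair.
3. Replace the sentence on additional outcomes with minimum detectable between-strategy differences for RVEF and 6MWT, stating which kind of SD is assumed.
4. Remove PVR, or name the endpoint actually listed (TPR).

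The cost is wording and slightly less favourable stated figures. Recruitment, design and analysis do not change.
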